### Data analysis

T tests and analyses of variance will be used to assess potential baseline difference in the outcome measures. Linear mixed-effects models will be used to estimate change utilising data available from participants at all time points. These models may be adjusted for clustering in the data due to repeated measures on the same individuals and due to the intervention being delivered across multiple sites.

Content analyses will be carried out on the survey data provided by DBT therapists which will inform the implementation evaluation.

An economic evaluation will be performed to assess the cost-effectiveness of DBT versus treatment-as-usual for the treatment of adults with BPD who engage in self-harm. The cost-effectiveness analysis will compare the relative costs and outcomes (effects) of the DBT intervention. All relevant costs from the perspective of the health care provider will be identified, measured and valued. Direct health service use will be measured by means of a resource use questionnaire. The relevant health effects will be measured in natural health units using recognised scales, for example, the Beck Depression Inventory. In addition, Quality Adjusted Life Years (QALY) will be calculated with the EQ-5D-5 L utility scores. An incremental Cost Effectiveness Ratio (ICER) will be calculated comparing the relative costs and outcomes. The economic evaluation will be conducted in line with the eight-step framework put forward by Drummond et al. [57].

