In line with best practice guidelines, and national mental health policy frameworks, a number of community services in Ireland endeavoured to establish DBT programmes in their locality. Prior to 2013, any such teams were driven by clinician interest and in many instances, failed to sustain as a result of systemic issues. Such issues included lack of management support and funding for training given that DBT had not been listed as a mandated treatment in Irish national health service plans. International research (e.g. [38, 39]) also highlight a number of factors that can impact on effective implementation of DBT. Examples of such barriers include lack of support from public mental health authorities and programme leaders, and absence of organisational support (including staff turnover, and funding for administration, training and supervision). Given positive research outcomes on effectiveness of DBT in a separate study across four sites in the south of Ireland [40], a National Office for Suicide Prevention (established specifically to drive suicide and self-harm prevention strategies in the public health service in Ireland) agreed to fund and support a project team to coordinate a multi-site implementation of DBT in community settings at a national level [41]. As a result, the National DBT Project, Ireland was established in 2013.

As no previous research has been conducted on a coordinated national implementation of DBT in a publically funded mental health system, it was deemed appropriate and necessary to comprehensively evaluate this implementation effort. The research study has three primary aims; first, to assess if individuals who participate in the DBT intervention will achieve positive outcomes when the intervention is delivered as part of a coordinated, multi-site implementation; second, to investigate if a coordinated implementation which addresses known implementation barriers will enable sustainable service provision; and third, to investigate whether it is cost effective to implement DBT versus treatment-as-usual in a publicly funded community mental health setting.

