### Study design

This study takes the form of a multi-site quasi-experimental design with non-equivalent groups. As the setting for this study is the publicly funded health system, staff have a responsibility to treat every individual who presents to the service. As a result, patients attending Community Mental Health Services who meet eligibility criteria for participation in DBT will be offered the intervention. At the onset of this study, there was no alternative system wide evidence-based intervention available for this client group that could have been used for comparison purposes. Additionally, in abiding with ethical guidelines and appropriate care of patients, neither is it possible to withhold treatment for individuals who meet criteria for participation in the intervention. Therefore, it was not possible to randomly allocate participants to a DBT intervention, comparable intervention or control group for the purposes of this study. Given this limitation, a treatment-as-usual comparison group was utilised which comprises of individuals who cannot access DBT in their area or who opt out of DBT as a treatment option (but continue to engage in routine care).

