### Sample size

It is anticipated that there will be a total of 442 participants across 16 sites in this research study over a four year period. Of the 312, it is estimated that 120 will be adults with a primary diagnosis of BPD attending Adult Mental Health Services across eight study sites. It is estimated that 96 participants will be adolescents with emotional and behavioural dysregulation (emerging borderline personality presentations) across eight study sites. As the adolescent’s caregiver also attends the skills training sessions, there will also be up to 96 parent/guardian participants. All DBT therapists (approximately 130 clinicians) who train as part of the National DBT Project, Ireland will be invited to participate in the research study.

The power calculation is based on the aim of identifying if the intervention is effective across multiple sites as part of a coordinated national implementation with adults and adolescents. It was decided to use a medium effect size of 0.5 according to Cohen [54] for the power calculation with an alpha level of 0.05. The primary outcome measure chosen for the power calculation is the Borderline Symptoms Checklist [55]. With an anticipated sample size of eight clusters per adult group with 15 patients per cluster, and an intracluster correlation coefficient of 0.01, the power to detect change over time is 92%. With an anticipated sample size of eight clusters per adolescent group with 12 patients per cluster, and an intracluster correlation coefficient of 0.01, the power to detect change over time is 86% [56].

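### The design has a treatment-as-usual comparator, but the first aim, the power and the effectiveness model are all about change over time, so background improvement could be reported as a DBT effect

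*Protocol article*

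**What the plan says.** All references are to the protocol article.

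- **Study design** describes a "multi-site quasi-experimental design with non-equivalent groups". The TAU group consists of "individuals who cannot access DBT in their area or who opt out of DBT as a treatment option". The Treatment-as-usual section under Participants repeats these two sources.
- **Background** gives the first of three aims as "to assess if individuals who participate in the DBT intervention will achieve positive outcomes". No comparator is mentioned in that aim.
- **Sample size** decides to "use a medium effect size of 0.5" on the Borderline Symptoms Checklist, "with an alpha level of 0.05". It reports 92% power for adults (eight clusters of 15) and 86% for adolescents (eight clusters of 12), ICC 0.01, both described as power for change over time.
- **Data analysis** begins with "T tests and analyses of variance will be used to assess potential baseline difference in the outcome measures" and continues "Linear mixed-effects models will be used to estimate change utilising data available from participants at all time points". The only adjustment mentioned is optional: "These models may be adjusted for clustering in the data due to repeated measures on the same individuals", and likewise for delivery across sites.
- **Data analysis**, economic part, does set DBT against TAU, for adults only.
- **Strengths and limitations** says a comparison group is hoped for, and that the study has enough power in both populations to answer whether DBT will produce positive outcomes.

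**The concern.** The aim, the powered quantity and the model target all point to change, while the design was built around a comparison. A pre-post change does not isolate what DBT contributes. Adults enter after a self-harm or suicidal episode in the six months before referral. Adolescents enter after such an act in the last 16 weeks or with chronic suicidal ideation. Concomitant care says medical and psychiatric treatment usually continues. Some improvement is therefore expected without any DBT effect.

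At stake is the main effectiveness conclusion. A significant fall in the DBT group could be reported as DBT producing positive outcomes, while the group recruited to show what happens without DBT has no stated part in that estimate. For adolescents, who are outside the economic comparison, the article states no analytic use of TAU at all.

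**Working it through.** **1. The plan's own power.** Inputs from Sample size: d = 0.5, alpha 0.05 (taken as two-sided), ICC 0.01, 8 clusters of m = 15 or 12.

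- Design effect = 1 + (m − 1) × 0.01: 1.14 for adults, 1.11 for adolescents.
- Effective n: 120/1.14 = 105.3; 96/1.11 = 86.5.
- Two independent groups of eight clusters each: noncentrality 0.5 × √(n_eff/2) = 3.63 and 3.29. With t on 2(8 − 1) = 14 df, power is **92.1%** and **86.3%**, which reproduces the stated 92% and 86%.
- One group, change of 0.5 SD of the change score: noncentrality 0.5 × √n_eff = 5.13 and 4.65. With 7 df, power is 99.2% and 97.7%, which does not match. If 0.5 is in baseline SDs, a one-group change matches only with a pre-post correlation of about 0.15, which is not stated.

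So the figures behave like a comparison of two equal independent groups, although the text calls them power for change over time.

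**2. Is there a second group in the sample size?** 120 adults + 96 adolescents + 96 parents/guardians + 130 therapists = 442, the stated total. No TAU patients remain. If the formula meant DBT versus TAU, an equal TAU group is missing. If it meant baseline versus later, the two time points were treated as independent.

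**3. What a pre-post test shows when DBT adds nothing.** Assumptions (the documents give none): background improvement δ in SD units, pre-post correlation r from 0.5 to 0.8, and ICC 0.01 applied to the change. Noncentrality = δ/√(2(1 − r)) × √n_eff, 7 df, two-sided 0.05. Example for adults with δ = 0.2: r = 0.5 gives 0.2/1.000 × 10.26 = 2.05, hence 43%; r = 0.8 gives 0.2/0.632 × 10.26 = 3.24, hence 79%.

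| Background improvement | 120 adults | 96 adolescents |
|---|---|---|
| 0.1 SD | 14–29% | 13–25% |
| 0.2 SD | 43–79% | 36–71% |
| 0.3 SD | 75–98.5% | 67–96% |

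The nominal rate is 5%.

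**4. Power of a DBT-versus-TAU contrast.** Planned DBT group; TAU size assumed, at the planned cluster size. Noncentrality = 0.5/√(1/n_eff,DBT + 1/n_eff,TAU), df = total clusters − 2.

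| Adults: TAU n | Power | Adolescents: TAU n | Power |
|---|---|---|---|
| 120 | 92% | 96 | 86% |
| 60 | 76% | 48 | 68% |
| 30 | 52% | 24 | 45% |

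No allowance is made for confounder adjustment or dropout.

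**5. Could baseline tests stand in for adjustment?** Suppose they compare DBT with TAU. For a true 0.3 SD imbalance with 120 DBT patients, a two-sided t test without clustering detects it 31%, 37% or 47% of the time with 30, 40 or 60 TAU patients (assumed sizes). A non-significant result would not show comparability.

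**The case against.** The strongest reply is that silence is being read as exclusion. A mixed model for change can carry a group-by-time term, the text does not rule one out, and an article commonly leaves model terms and covariates to a fuller plan. The first aim has no comparator, so a change estimate answers it as worded. The article also openly calls the lack of randomisation a limitation.

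Much of this stands, and it rules out several stronger readings that a reader might infer:

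- *TAU is excluded from the effectiveness analysis.* Not supported: its role is unstated. The two-group behaviour of the power figures even suggests that a comparison may have been in mind.
- *Baseline t tests are the only between-group analysis.* Not supported: the article does not say which groups they compare, and the adult economic evaluation compares DBT with TAU on costs and effects.
- *Confounding biases the change estimate.* Between-group confounding cannot bias a DBT-only change. It matters once TAU is brought in, particularly for patients who opted out.
- *Regression to the mean can be sized from the entry criteria.* It cannot: entry requires a persistent pattern of self-harm and sets no symptom-score threshold, and baseline is the week before the first skills session, so some reversion may precede it.
- *The adjustment data are already held for both groups.* Not shown: emergency visits and admissions are on a therapist-completed form described for DBT patients.

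What the reply does not remove is the conflict between what the article does fix. Aim, powered quantity and model target are all change, the design is comparative, and the stated conclusion is about what DBT produces.

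**Conclusion.** The point holds as a mismatch between a comparative design and an effectiveness estimate defined as change over time. Unless a DBT-versus-TAU contrast is named, improvement that would have occurred anyway can be reported as effectiveness. With 120 adults and an assumed background improvement of 0.2 SD, that happens about 43% to 79% of the time when DBT adds nothing. Those rates depend on the assumed drift and correlation; the mismatch in the text does not. The claim of sufficient power is not supported for a DBT-versus-TAU contrast, because no TAU number is given. This should be settled before effectiveness is reported.

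**What to change.** In Data analysis:

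- Name the DBT-versus-TAU group-by-time contrast in the mixed model as the effectiveness estimate at end of programme (12 months after baseline for adults, 16 weeks for adolescents), with the same assessment intervals for TAU. Fit adults and adolescents separately.
- Account for the baseline value of the outcome and state how. Difference in change and adjustment for baseline can disagree in non-equivalent groups, so one should be primary.
- Adjust for prespecified prognostic variables measured in both groups, for example the baseline self-report scales, whatever the baseline tests show. Use emergency visits and admissions only if they are recorded for TAU.
- Make the site-clustering adjustment definite.
- Label within-DBT change as uncontrolled and descriptive.

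In Sample size and in Strengths and limitations, say which comparison the 92% and 86% refer to, give the expected TAU numbers, and restate the power. If too few TAU patients are obtained, limit the conclusion to uncontrolled change.

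The cost is mostly wording and some analysis, provided TAU patients are recruited and measured on the same scales and schedule. The interval will be wider than for uncontrolled change, and the stated power will look less favourable unless TAU matches DBT in size.

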### Ethical principles

The participation in the study is voluntary. Participants are informed that if they decide not to participate in the study that this will not affect their treatment in any way. Participants are informed that they can withdraw their participation at any time without providing a reason. All participants are asked to sign an informed consent form.

### Ethics approval

Research ethics approval was sought and obtained from all relevant research ethics committees at the multiple sites of this research study.

## Discussion

The study protocol is outlined here to offer clinicians and researchers in publically funded health systems an opportunity to consider the methodological quality of this effectiveness study with a critical view. Publicly funded health systems may benefit from considering how the proposed protocol could be applied to outpatient mental health settings which treat individuals with emotional and behavioural dysregulation. There are a limited number of effectiveness studies looking at standard stage 1 DBT in public mental health settings. Research on effectiveness of DBT when implemented in a coordinated manner could provide an important contribution to improving routine mental health care for patients with BPD.

The protocol also offers clarity on quality, quantity and experience of participating in a coordinated implementation of DBT at a national level. This could potentially provide evidence on how best to overcome barriers to implementation in publicly funded health systems.

The economic evaluation which is carried out as part of this research study will provide important information on the cost of BPD illness to a public health service which will facilitate international comparison. In addition, evaluating the cost of implementing DBT in a coordinated manner in comparison to treatment-as-usual will provide support for the value of robust application of an evidence-based intervention which is also in line with best practice guidelines.

One of the limitations in previous research on DBT effectiveness is the variability in outcome measures utilised to assess clinical effectiveness. This protocol specifically matches outcome measures to treatment targets for DBT in an attempt to create a standardised battery of measures that can be applied across any research setting. Evidence on effectiveness, resource utilisation and feedback from both patients and therapists will shape systemic culture change in how we treat individuals with chronic self-harm and suicidal behaviours.

As this study is carried out in a publicly funded health system, this study considers how this treatment might be applied to multiple patient groups, in this case adults and adolescents. No study to our knowledge has reported on the effectiveness of the 16-week DBT programme as described by Miller and colleagues [28] for adolescents in community settings so it is anticipated that the results of this study will also contribute to this gap in the literature.

### Strengths and limitations

As this study is carried out in a real-world setting, DBT therapists do not have dedicated time to devote to research related tasks, as would be the case in a clinical research trial. Therapists are therefore participating in a voluntary capacity in addition to daily routine and regular professional practice. Given the nature of this comprehensive evaluation, it is anticipated that full compliance with the data collection protocol may not always be possible with competing clinical demands. In an effort to offset this risk, each team will be supported by a member of the coordinating team who will provide guidance and assistance with the research evaluation where possible. In addition, in real-world settings, therapists have a mixed qualification and skill set in relation to research related tasks in contrast to those specifically recruited to support clinical research trials.

One of the strengths of this study is that a dedicated research team has been recruited to coordinate and support this multi-site research evaluation. This was done in an effort to reduce experimenter bias which may be present if clinicians who are working with patients conduct data collection. It is anticipated that having a dedicated research team will also increase the reliability and quality of data collection at agreed time points, and will allow for follow-up data collection to maximise dataset completeness. Having a researcher assigned to each team who will support clinicians during the process of the study will also potentially increase response rates and dataset completeness. Feedback will be provided to each participating service and updates will be provided regarding recruitment status on a regular basis by the research team. At the end of the study, summary reports of the results for each individual site, in addition to the pooled data analysis, will be provided to each team to provide feedback to clinicians and aid service planning. The outlined difficulties with regard to real-world research needs to be managed if researchers and clinicians are to work towards increasing external validity i.e. the effectiveness of an intervention in a publicly funded health system implemented in a manner that is sustainable over time.

Although one of the challenges in conducting effectiveness studies is inclusion of data from a control group, the current study hopes to obtain a comparison group by utilising data collected from treatment-as-usual patients in areas with no DBT provision or where patients opted out of treatment. While real-world challenges prohibit a randomised controlled design in a community setting, there is still merit in having a comparison group who do not receive treatment for the purposes of the evaluation.

The comprehensive research evaluation includes both quantitative and qualitative feedback from multiple perspectives including that of the patient, their family member (in the case of adolescents) and their therapist. Such comprehensive and robust evaluation will serve to inform the real value of DBT as an intervention when delivered in a publicly funded health setting and will potentially serve to inform our system to refine and increase sustainability of service provision over time.

The advantage of having a multi-site study is that it yields a larger sample size. A strength of this study is that we have sufficient power in both the adult and adolescent populations to answer the research question as to whether DBT, if delivered in a coordinated manner, will produce positive outcomes for patients in a publicly funded health system.

This study will potentially provide evidence to endorse DBT as an evidence-based treatment that can be effectively delivered in community settings for high risk individuals. This approach will potentially lend itself to better coordinated interventions and public health system changes that may reduce the need for repeated emergency department attendances and protracted periods of acute hospitalisations.

## Abbreviations

BDI: Beck Depression Inventory
BHS: Beck Hopelessness Scale
BPD: Borderline Personality Disorder BSL Borderline Symptom List
CBT: Cognitive Behaviour Therapy
DBT: Dialectical Behaviour Therapy
NICE: National Institute for Health and Care Excellence
QOL: Quality of Life
